## Experimental steps and stages

The present study includes a 2-week cleaning period and a 8-week double-blind randomized treatment period. After treatments for 2 weeks, 4 weeks and 8 weeks, interviews are needed. There is a safety observation period with 56 weeks after finishing of the double-blind, randomized treatment period. One interview is needed to be done every 8 weeks.

The informed consents should be signed by the subjects before screening.

### Screening/cleaning periods (Interview 1, -3 weeks ~ 0 week)

Three weeks before the treatment with the research drug is given, and before the subjects take placebo (that is -3 weeks to -2 weeks), the following screening assessment projects should be completed:

- - Demographic data: including gender and ages (date of birth) of the subjects;
  - Height, weight, waist circumference, smoking and drinking status;
  - Collecting of the disease history: inquire and record the history of hypertension of the subjects (including the disease time of the blood pressure and levels of hypertension), family history, complications/diseases and their treatment histories, other previous disease and treatment history, allergic history;
  - Physical examination: physical examinations of all body systems are conducted;
  - Resting sitting blood pressure and heart rate measurements;
  - Laboratory and auxiliary examinations: including urine pregnancy test (limited to women of childbearing age), whole blood test, urine routine test test, liver function, renal function, fasting blood glucose, blood lipid, blood electrolyte and 12-lead electrocardiogram.

Preliminary screening of low and middle risk patients with primary hypertension, and basically meeting the inclusion criteria but not with the exclusion criteria, the patients were into the placebo washout period of 2 weeks (that is -2 weeks ~ 0 week) with distribution and taking 2 weeks of placebo and diary cards of the subjects at the same time.

In addition, recording the signed informed consent and the adverse events and concomitant treatment during placebo wash out period.

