
**Experimental flow chart**

|  | **Screening and cleaning periods** | | | **Baseline period** | **The treatment period (window period ± 3 days)** | | | **Safety observation period 5 (window period ± 7 days)** | | | |
| --- | --- | --- | --- | --- | --- | --- | --- | --- | --- | --- | --- |
| **Screenig** | | **Cleaning** |
| Interview times | **1** | | | **2** | **3** | **4** | **5** | **6-8** | **9** | **10-11** | **12** |
| Interview time (week) | **－3～－2** | **－2～0** | | **0** | **2** | **4** | **8** | **9-32** | **40** | **48-56** | **64** |
| Signing written informed consent | **X** |  | |  |  |  |  |  |  |  |  |
| Collecting Medical History | **X** |  | |  |  |  |  |  |  |  |  |
| Physical examination | **X** |  | |  |  |  | **X** | **X6** | **X** | **X6** | **X** |
| Blood pressure and heart rate in sitting position | **X** |  | | **X** | **X** | **X** | **X** | **X** | **X** | **X** | **X** |
| Auditing inclusion/exclusion criteria | **X** |  | | **X** |  |  |  |  |  |  |  |
| Urine pregnancy test 1 | **X** |  | |  |  |  | **X** |  |  |  | **X** |
| Routine blood test 2 | **X** |  | |  |  |  | **X** | **X6** | **X** | **X6** | **X** |
| Routine urine test 3 | **X** |  | |  |  | **X** | **X** | **X6** | **X** | **X6** | **X** |
| Liver function（ALT、AST、  TBil） | **X** |  | |  |  | **X** | **X** | **X6** | **X** | **X6** | **X** |
| Renal function（Bun、Cr、  Ua） | **X** |  | |  |  | **X** | **X** | **X6** | **X** | **X6** | **X** |
| Blood fat（TG、TC、HDL、LDL） | **X** |  | |  |  |  | **X** | **X6** | **X** | **X6** | **X** |
| Fasting blood-glucose（FPG） | **X** |  | |  |  |  | **X** | **X6** | **X** | **X6** | **X** |
| Blood electrolytes（K、Na、  Cl） | **X** |  | |  |  | **X** | **X** | **X6** | **X** | **X6** | **X** |
| 12 electrocardiograph（ECG） | **X** |  | |  |  |  | **X** |  | **X** |  | **X** |
| The drug release of the cleaning period 4 | **X** |  | |  |  |  |  |  |  |  |  |
| The drug recovery of the cleaning period |  |  | | **X**4 |  |  |  |  |  |  |  |
| 收Release and recovery of the research drugs |  |  | | **X** | **X** | **X** | **X** |  |  |  |  |
| Drug release and recovery of the safety observation period |  |  | |  |  |  | **X** | **X** | **X** | **X** | **X** |
| Release, recovery and transcription of diary cards of the subjects | **X** | **X** | | **X** | **X** | **X** | **X** |  |  |  |  |
| Recording concomitant medication | **X** | **X** | | **X** | **X** | **X** | **X** | **X** | **X** | **X** | **X** |

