There was no significant difference in various indexes of liver functions before and after treatment and between groups, and there was no case with dysfunction of liver after treatment in the group of Allisartan Isoproxil (240 mg). After treatment with Allisartan Isoproxil (240 mg) for 4 weeks and 8 weeks, the level of creatinine was decreased (statistically significant); After treatment for 4 weeks, levels of uric acid in the groups of various doses of Allisartan Isoproxil and the group of Losartan (50 mg) were all reduced (statistically significant). After treatment for 8 weeks, levels of uric acid in the groups of Allisartan Isoproxil (80 mg, 240 mg) and the group of Losartan (50 mg) were all decreased (statistically significant); but there was no significant difference between the groups. After treatment for 4 weeks, levels of serum sodium and chlorine both increased in the group Losartan (50 mg), which was significantly different from that of the groups with different doses of Allisartan Isoproxil when comparing, but there was no significant difference between these groups in 8 weeks; the concentration of potassium was elevated after treatment with Allisartan Isoproxil (80 mg, 240 mg) for 4 weeks (statistically significant). The level of serum potassium was increased after treatment only with Allisartan Isoproxil (80 mg) for 8 weeks, but there was no significant difference between groups.

Of all the subjects with normal electrocardiogram before treatment, there were 2 patients had abnormal electrocardiogram treated for 8 weeks, and the related adverse events were recorded, which was diagnosed by 1 researcher that it was not related to the research drug, while another research believed that it was related to the research drug. There was no significant difference in the resting heart rate between different groups after treatments for 2, 4, 8 weeks.

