### Baseline period (Interview 2, 0 week)

After the subjects taking the placebo for 2 weeks, the following aspects should be conducted:

- - Rest sitting blood pressure and heart rate were measured: the measurement method is the same as that of the screening period;
  - Auditing the inclusion/exclusion criteria, the qualified subjects were distributed with random numbers according to the order of grouping from small to large order (i.e. drug number);
  - Distribution of drug of the first ~ the second week treatment period (including 3 days of alternate drug) according to the random numbers issued;
  - Recovery of the research drugs in the placebo washout period of 2 weeks;
  - Transfer and recording of diary cards of subjects;
  - Recording adverse events and concomitant treatments.

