## Combined application of drugs

Combined application of Losartan potassium with potassium supplement pills or isokalaemic diuretic (such as spironolactone, triamterene, amiloride etc.) may cause the increase in serum potassium level. Losartan potassium can increase the toxicity of lithium. Fluconazole can inhibit the transformation of losartan potassium into active metabolites of EXP3174. Similar to other anti hypertensive drugs, the non-steroidal anti-inflammatory drug indometacin can decrease the antihypertensive effects of losartan potassium. Rifampicin had obvious induction roles to the present drug and its metabolites EXP3174, reducing AUC and serum concentration of the drug and decreasing its efficacy. Ephedra contains ephedrine and pseudoephedrine, which can reduce the antihypertensive effects of the drugs. For the patients with hypertension treated with losartan potassium, formulations containing ephedra should be avoided.

EXP3174 is the active medicinal product of ALS-3. The active metabolites of losartan potassium playing main pharmacodynamic actions are also EXP3174. The matters needing attention in the specification of losartan potassium have very important reference value to ALS-3. Therefore, the above drugs refered to are not allowed to be used in the study period (including the cleaning period of 2 weeks), and any other drugs for treating hypertension are prohibited at the same time.

The interaction of drugs in the clinical application of Allisartan Isoproxil that may happen has not been studied.

All the concomitant medications were recorded in the corresponding position of the case report form.

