## Statistical methods

### Aalysis method

Statistical analysis using SAS9.13 statistical analysis software for calculation. Quantitative description of the calculation of mean and standard deviation, median, minimum value, maximum value. Classification index described by number and percentage of cases.

Completion of the study will be carried out descriptive statistics on the demographics and baseline characteristics were compared between the two groups in a balanced analysis between groups.

Analysis of the main outcome measures: the main efficacy index will adopt non inferiority test. In addition, also calculate each subject after 8 weeks of treatment, DBP decreased and the seat value groups (mean standard deviation, median, minimum and maximum), groups were compared using analysis of variance center effect considered.

Analysis of secondary efficacy indicators: in principle does not consider the center effect, by using variance analysis, chi square test or nonparametric statistical method for comparison between groups.

Analysis of safety evaluation, safety evaluation included adverse events / ADR / important adverse events or serious adverse events, physical examination and laboratory examination and a 12 lead electrocardiogram. Cases of adverse events during the detailed description of test, summary comparison of incidence of adverse events between the two groups. Statistical description and index of laboratory examination and necessary changes were compared between the two groups. A detailed description of laboratory indexes was normal before treatment after treatment of abnormal.

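### The only pre-treatment laboratory and ECG values predate the placebo washout, so before/after safety readings may mix withdrawal of an earlier drug with the effect of the study drug

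*Protocol*

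**What the plan says.** Section 5.3.1 (Interview 1) sets the timing of the screening tests: "before the subjects take placebo (that is -3 weeks to -2 weeks), the following screening assessment projects should be completed". The panel includes "liver function, renal function, fasting blood glucose, blood lipid, blood electrolyte and 12-lead electrocardiogram".

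Section 5.3.2 (Interview 2, week 0, after two weeks of placebo) lists "Rest sitting blood pressure and heart rate were measured: the measurement method is the same as that of the screening period". It lists no laboratory test or ECG. Eligibility is audited again there: "Auditing the inclusion/exclusion criteria, the qualified subjects were distributed with random numbers". The flow chart agrees: the laboratory and ECG rows are marked at Interview 1 and blank at Interview 2. The next samples are at week 4 (urine, liver, renal, electrolytes) and week 8 (full panel and ECG).

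Section 9.1.2 treats this one early sample as the pre-treatment value. Section 8.1 defines a post-washout baseline, but for blood pressure only.

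Section 7.2 says that the listed interacting drugs are "not allowed to be used in the study period (including the cleaning period of 2 weeks"), and it bars other antihypertensives as well. It does not mention the screening week.

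For analysis, Section 11.4.1 plans an account of values that go from normal to abnormal, in imperfect translation: "A detailed description of laboratory indexes was normal before treatment after treatment of abnormal". The Protocol summary says laboratory differences between the arms are compared only where judged necessary.

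**The concern.** Blood pressure is compared with an off-drug value; the laboratory and ECG measures may not be. If a patient is sampled on a diuretic, ACE inhibitor, ARB or beta-blocker and then stops it for the washout, the pre-treatment potassium, creatinine, uric acid or lipid value belongs to a different drug state. A later change can then reflect stopping the old drug. Equally, a real effect of the study drug can be hidden because the old drug had already moved the marker.

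These measures matter here. Section 9.1.2 gives renal toxicity in animals as a reason for the monitoring. The earlier phase II trial, as reported in Section 1.2, was read partly through within-arm changes: "the concentration of potassium was elevated after treatment with Allisartan Isoproxil (80 mg, 240 mg) for 4 weeks". Creatinine and uric acid changes were reported in the same way. The 56-week phase has no control arm, so nothing within it separates the two sources of change.

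**Working it through.** The plan states no figure on this point, and its sample-size calculation is not involved. The check compares the schedule, the drug ban and the planned analyses.

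**1. Age of the sample at Interview 2.** Screening falls up to 7 days before placebo starts (Section 5.3.1). The washout visit is at 14 ± 3 days (flow chart, note 4).
- Shortest: 0 + (14 − 3) = 11 days.
- Longest: 7 + (14 + 3) = 24 days.

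**2. Can the drug state change in between?** No section says outright that earlier antihypertensives may be taken at screening. The following point that way:
- Section 7.2 names the washout as the early part of the banned period and not the screening week.
- A washout presupposes something to wash out.
- The diagnostic criteria in Appendix 1 count patients already on antihypertensives as hypertensive.
- In the earlier trial (Section 1.2, research methods), patients stopped their original antihypertensives and took placebo for two weeks.

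Against this, exclusion 15 (drugs affecting blood pressure) has no time window.

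**3. Do these markers move with such drugs?** By the protocol's own account, yes. Section 1.2 reports lower uric acid at weeks 4 and 8, and higher sodium and chloride at week 4, on losartan 50 mg. Section 7.2 warns of raised potassium when losartan is combined with potassium supplements or potassium-sparing diuretics.

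**4. Size, using potassium as the example.** Let *f* be the share treated at sampling, *s* the absolute shift on withdrawal, and *u* the fraction of treated patients who shift in one direction, the rest shifting the other way. With no study-drug effect:

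spurious mean within-arm change = *f* × *s* × (2*u* − 1)

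None of the three is in the protocol. Assume *f* = 0.30 to 0.70 and *s* = 0.2 to 0.3 mmol/L.
- All shift the same way (*u* = 1): 0.30 × 0.2 = 0.06, to 0.70 × 0.3 = 0.21 mmol/L.
- Split 70/30 (2*u* − 1 = 0.4): 0.06 × 0.4 = 0.024, to 0.21 × 0.4 = 0.084 mmol/L.
- Split 50/50 (2*u* − 1 = 0): 0.

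The range therefore starts at zero, and the documents do not narrow it. Cancellation applies to the mean only: an individual patient's move from normal to abnormal does not cancel against another's.

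**5. Between the arms.** Randomisation gives both arms the same expected spurious change, so the expected difference is 0. The cost is added noise, not bias.

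**6. Is there a cleaner value already collected?** Patients on placebo in the double-blind period have a full panel and ECG at Interview 5, before their first active dose. The earliest such sample, counted from the start of placebo, is 11 + (56 − 3) = 64 days, or 64/7 = 9.1 weeks.

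**The case against.** The strongest reply is that the premise is inferred. The ban in Section 7.2 is worded inclusively and gives no start date. Exclusion 15, audited at Interview 1, could be read to keep out anyone still on an antihypertensive. Section 1.1 describes observing low- and medium-risk patients before deciding on medication, so the treated share may be small. This stands as a limit: prior drug use at sampling is a strong inference, not a stated fact.

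A reader might also infer that the before/after changes would produce false statistical significance, by turning assumed potassium shifts into multiples of a standard error. The documents do not support that. Such a figure needs every treated patient to shift the same way, and it describes a within-arm test that this protocol does not plan. Within-arm testing is reported for the earlier trial only.

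Nor is the randomised safety comparison biased. The placebo arm goes through the same washout, so its normal-to-abnormal account shows the same artefact and can serve as the reference, provided that the two arms are read together.

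It can also be said that baseline definitions and covariates belong in a statistical analysis plan, which is not at hand, and that investigators may add safety tests at any time (flow chart, closing note). Both are true. But the visit schedule is fixed in the protocol, an analysis plan cannot create a week-0 sample, and discretionary tests do not give a systematic baseline.

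**Conclusion.** The point holds in limited form, with minor to moderate priority. The timing is certain: the sole scheduled pre-treatment laboratory and ECG values precede the washout, and none is taken at week 0. For patients still on an earlier antihypertensive at Interview 1, the normal-to-abnormal account and any before/after reading of the 56-week phase mix withdrawal of the old drug with the effect of the study drug.

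This rests on the inference that some patients are so treated. The magnitude cannot be fixed, because the treated share, the drugs involved and the direction of their effects are not given. The 8-week between-arm comparison is unbiased, though noisier, and the primary diastolic endpoint is untouched because its baseline follows the washout.

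**What to change.** 1. In Section 11.4.1, base the 8-week laboratory conclusions on the between-arm difference adjusted for the screening value, as a planned comparison and not one made at discretion. Show the normal-to-abnormal account by arm and by recorded prior antihypertensive use. The clearest source for the latter is the concomitant-medication record, which the flow chart starts at Interview 1; the hypertension-history item in Section 5.3.1 does not name treatment.
2. For patients who took placebo in the double-blind period, use the existing week-8 panel and ECG as the pre-drug baseline for the 56-week phase.

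Both are changes of analysis wording on data already collected. The second helps only former placebo patients; those first randomised to active drug would still have no scheduled off-drug value.

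3. Optionally, add a small blood panel (potassium, sodium, creatinine, uric acid, liver tests) at the existing Interview 2 visit, before the first randomised dose, and make it the safety baseline for those measures. This covers both arms. The cost is laboratory work for about 260 patients; the sample size does not change.

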### Baseline period (Interview 2, 0 week)

After the subjects taking the placebo for 2 weeks, the following aspects should be conducted:

- - Rest sitting blood pressure and heart rate were measured: the measurement method is the same as that of the screening period;
  - Auditing the inclusion/exclusion criteria, the qualified subjects were distributed with random numbers according to the order of grouping from small to large order (i.e. drug number);
  - Distribution of drug of the first ~ the second week treatment period (including 3 days of alternate drug) according to the random numbers issued;
  - Recovery of the research drugs in the placebo washout period of 2 weeks;
  - Transfer and recording of diary cards of subjects;
  - Recording adverse events and concomitant treatments.

### Treatment period (Interview 3, 2 weeks ± 3 days)

After the subjects taking 2 weeks of the research drugs in the double-blind randomized treatment period, the following asepects are needed:

- - Resting sitting blood pressure and heart rate measurement: the measurement method is the same as that of the screening period;
  - Distribution of drug of the third ~ the fourth week treatment period (including 3 days of alternate drug) according to the random numbers issued;
  - Recovery of the research drugs in the placebo washout period of the first and the second week;
  - Transfer and recording of diary cards of subjects;
  - Recording adverse events and concomitant treatments.

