### The treatment period (Interview 4, 4 weeks ± 3 days)

After the subjects taking 4 weeks the research drugs in the double-blind randomized treatment period, the following aspects should be done:

- - Resting sitting blood pressure and heart rate were measured: the measurement method is the same as that of the screening period;
  - Laboratory examinations: urine routine test test, liver function, renal function and serum electrolyte;
  - According to the distributed random numbers, the research drugs for the fifth ~ eighth week treatment period were given (including 6 days of alternative drug);
  - Recovery and counting of the third ~ fourth week remaining reserch drugs;
  - Transfer and recording of the diary cards of subjects;
  - Recording adverse events and concomitant treatments.

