### The safety observation period (Interview 6-11, 9-56 weeks, every interview for 8 weeks, the window period ± 7 days)

In order to observe the long-term efficacy and safety of the research drugs, all the subjects would participate in the safety observation period research of 56 weeks voluntarily after they finish the double-blind randomized study of 8 weeks, during which each subject will receive 240 mg Allisartan Isoproxil tablet treatment once a day, and the subjects should visit the doctor every 8 weeks:

- - Resting sitting blood pressure and heart rate were measured: the measurement method is the same as that of the screening period;
  - Laboratory examinations: urine routine test test, liver function, renal function and serum electrolyte (if the laboratory indicators are abnormal in the observation of former 8 weeks, please reexamine; if it is normal, please judge freely whether reexamination is necessary according to the circumstances);
  - Distribution of Allisartan Isoproxil tablets for 9 weeks doses;
  - Residual drug recovery of the past 8 weeks and counting;
  - Recovery, transfer and recording of the diary cards of the subjects;
  - Recording adverse events and concomitant treatments.

The interview 9, namely the interview of the subjects taking the research drugs for 32 weeks during the safety observation period, in addition to the above items, the following aspects are also needed to be conducted:

- - Physical examination: physical examination of all body systems including weight;
  - Laboratory examinations: urine routine test test, liver function, renal function and serum electrolyte;
  - Laboratory and auxiliary examinations including whole blood test, fasting blood glucose, blood lipid, blood electrolyte and a 12-lead electrocardiogram.

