### Packaging of drugs during the treatment period

The packaging of the research drugs include large packaging, big packaging, middle packaging and small packaging.

Each of the large package (big bog) includes the research drugs for 8 weeks randomized double-blind treatment period on a subject, which is labeled as "Allisartan Isoproxil clinical trial drug (the third – the tenth week), containing 4 large packages (a total of 68 plates).

Each of the large package (small bag) includes the research drugs for 2 weeks of the treatment period on a subject, which is labeled as "Allisartan Isoproxil clinical trial drug (the x – the x week), containing 3 middle packages (a total of 17 plates).

The middle packag (Aluminium plastic composite film bags) is divided into two kinds: one is "7 days of medication" (a total of 7 plates) and another is a "3 days of alternative medicine" (a total of 3 plates).

Each small packag is 1 aluminum plate. Each plate contains Allisartan Isoproxil tablet/placebo of 3 tablets, which is 1 day of medication.

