## Drug distribution and checking

The cleaning period drugs for 2 weeks were distributed by the research physician in charge of Drug Administration to the preliminarily screened eligible subjects, which was recorded. After finishing the cleaning period for 2 weeks, the physicians were responsible for the recovery and counting the residual drugs and empty packaging inventory of the selected subjects.

After the cleaning period, the included subjects were further screened for the qualified subjects according to the research protocol. According to the selected sequence from small to large, random numbers (i.e. drug number) were distributed, and 1 ~ 2 weeks of the research drugs corresponding to the drug number in the randomized double-blind treatment period were distributed. The amount of the distributed drugs was recorded.

After finishing the treatment for 2 weeks, the subjects were interviewed by returning to the research center according to the research protocol. The research physician were responsible for the recovery and counting of the remaining drug number and empty package of all subjects, and 3-4 weeks randomized double-blind research drugs in the treatment period were distributed. The number of recovery and distributed drugs were recorded.

After finishing the treatment for 4 weeks, the subjects were interviewed by returning to the research center according to the research protocol. The research physician were responsible for the recovery and counting of the remaining drug number and empty package of all subjects, and the fifth to the eighth week randomized double-blind research drugs in the treatment period were distributed. The number of recovery and distributed drugs were recorded.

After finishing the treatment for 8 weeks, the subjects were interviewed by returning to the research center according to the research protocol. The research physician were responsible for the recovery and counting of the remaining drug number and empty package of all subjects, and the ninth to the sixteenth week randomized double-blind research drugs in the treatment period were distributed. The number of recovery and distributed drugs were recorded.

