In the 56 weeks of safety observation period, the subjects were interviewed by returning to the research center according to the research protocol. The research physician were responsible for the recovery and counting of the remaining drug number and empty package of all subjects, and the ninth to the sixteenth week randomized double-blind research drugs in the treatment period were distributed. The number of recovery and distributed drugs were recorded.

After finishing the 56 weeks of safety observation period, the subjects were interviewed by returning to the research center according to the research protocol. The research physician were responsible for the recovery and counting of the remaining drug number and empty package of all subjects.

Whether the subjects complete the study or not, the untaken drugs and empty packaging must be returned to the researchers. Researchers should keep all the returned drugs and empty packaging for the recording until the CRO company together recovery of the not distributed products.

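### Drug dispensed at Interview 3 does not cover the longest interval that the Interview 3 and 4 windows allow, so an in-window patient can miss up to three doses before the week-4 reading

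*Protocol*

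**What the plan says.** - **Windows, double-blind period.** The section headings tie each visit to a study week: "Treatment period (Interview 3, 2 weeks ± 3 days" and "The treatment period (Interview 4, 4 weeks ± 3 days". The Experimental flow chart agrees, with columns at weeks 2, 4 and 8 under "The treatment period (window period ± 3 days".
- **Supply.** Section 5.3.3 gives, at Interview 3, "Distribution of drug of the third ~ the fourth week treatment period (including 3 days of alternate drug". Section 6.4.2 describes the two-week pack as "containing 3 middle packages (a total of 17 plates", and one plate is one day of medication. Section 5.3.4 gives weeks 5-8 plus 6 reserve days at Interview 4.
- **Recovery.** At the 2-week visit, section 6.5 has the physician carry out "recovery and counting of the remaining drug number and empty package of all subjects, and 3-4 weeks randomized double-blind research drugs". The Protocol summary likewise lists recovery of the remaining week 1-2 drug at Interview 3. At the end of section 6.5, "the untaken drugs and empty packaging must be returned to the researchers".
- **Safety period.** Sections 5.3.5 and 5.3.6 dispense nine weeks of drug per visit ("Distribution of Allisartan Isoproxil tablets for 9 weeks doses"), with visits every 8 weeks ± 7 days. Section 5.3.7 puts Interview 12 at week 64 ± 7 days.
- **Endpoint and compliance.** Section 8.1 defines trough as 23 to 26 h after the morning dose. Appendix 2 has blood pressure read between 8:00 and 10:00, before that day's dose. Section 7.3 sets compliance limits of 80% and 120%.

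**The concern.** The three reserve days at Interview 3 allow for a late Interview 4. They do not also allow for an early Interview 3, and the surplus plates that an early visit leaves over are collected. A patient who follows every instruction can therefore run out of drug before the week-4 visit.

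The week-4 trough changes in DBP and SBP and the week-4 effective rate are secondary endpoints (section 8.2), and section 11.2 allows last observation carried forward in the full analysis set. A reading taken after missed doses is not a trough as defined. Missed plates can remove drug effect only in the active arm, so any bias runs towards no difference.

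**Working it through.** **The plan's own counts.** Two-week pack: 7 + 7 + 3 = 17 plates. Eight-week box: 4 × 17 = 68 plates. Both agree with section 6.4.2. Interview 4 supply: 28 + 6 = 34. Safety-period supply: 9 × 7 = 63 days. The last figure is inferred, because no plate count is given for that period and its label is marked as pending in Appendix 3.

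**Longest in-window interval** = (next nominal day + its window) − (this nominal day − its window), compared with the daily doses dispensed and no carry-over. The last two rows assume windows anchored to study weeks.

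| Interval | Earliest start | Latest end | Days | Doses | Short |
| --- | --- | --- | --- | --- | --- |
| Interview 2 to 3 | 0 | 17 | 17 | 17 | 0 |
| Interview 3 to 4 | 11 | 31 | 20 | 17 | 3 |
| Interview 4 to 5 | 25 | 59 | 34 | 34 | 0 |
| Interview 5 to 6 | 53 | 119 | 66 | 63 | 3 |
| Each later safety interval (e.g. 6 to 7) | 105 | 175 | 70 | 63 | 7 |

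**Timing at Interview 4.** The reading precedes the visit-day dose, so that dose is taken to come from the new pack. The 17 plates then cover days 11 to 27, and days 28, 29 and 30 have none. The reading on day 31 is 4 × 24 = 96 h after the last dose. If the first new plate is taken the next morning instead, the shortfall before the reading is 2 days and the day-11 dose is missed as well.

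**Cause.** Up to the latest Interview 5 (day 59), 59 doses are needed and 68 plates are packed. The gap comes from the split by visit together with the take-back step, not from too little drug overall.

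**Compliance.** Over the worst interval, 17/20 = 85%, above the 80% limit.

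**How often.** Each window has 7 days, so Interviews 3 and 4 give 7 × 7 = 49 day pairs. The interval exceeds 17 days in 3 pairs by one day, 2 pairs by two days and 1 pair by three days: 6/49 = 12.2%. With assumed weights 1-2-3-4-3-2-1 around the nominal day (sum 16), the share is (10 + 4 + 1)/256 = 15/256 = 5.9%. On uniform visits the safety-period shares are 6/105 = 5.7% for Interview 5 to 6 and 28/225 = 12.4% for each later interval.

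**Upper bound on attenuation.** Take the planning difference of 3 mmHg (section 11.1) as the week-4 difference, and assume the effect is wholly lost in every affected patient: 0.122 × 3 = 0.37 mmHg on uniform visits, and 0.059 × 3 = 0.18 mmHg on clustered visits.

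**The case against.** Four points on the other side carry weight.

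1. **The primary endpoint.** A reader might infer that the primary result is damaged. Interview 4 to 5 needs at most 34 doses and 34 are given, so the week-8 reading is covered. The carry-forward route is negligible: with the full 20% loss, all of it carrying week 4 forward, the bound is 0.20 × 0.122 × 3 = 0.07 mmHg. The early-exit visit (section 5.3.8) also asks for a blood pressure reading, which would usually replace the week-4 value. This point stands.

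2. **The safety period.** A reader might take a 7-day gap there as established. Visits every 8 weeks ± 7 days can be read as running from the last visit. The maximum is then 56 + 7 = 63 days, exactly the nine weeks dispensed. The flow chart's ranges for Interviews 6-8 and 10-11 leave room for this. Against it, lateness could build up over seven intervals to 7 × 7 = 49 days, which conflicts with week 64 ± 7 days. The text does not settle the matter. For Interviews 3 and 4 the headings and flow chart do settle it: they name study weeks.

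3. **Size.** The 12% needs uniform, independent visits, and 96 h applies to 1 day pair in 49. Complete loss of effect is not shown. The plasma half-life in section 1.2 does not measure blood pressure effect. In the earlier phase II study a third of the dose (80 against 240 mg) still gave week-4 DBP falls of 6.96 against 8.39 mmHg, though these are uncontrolled changes. The 0.37 mmHg is therefore a ceiling.

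4. **Detection.** It would be wrong to call the interruptions unrecorded. Plates are counted and diary cards collected in the double-blind period, Appendix 2 already asks for readings 24 h after dosing, and the list of serious violations for the per-protocol set stays open until data audit. A long interval can be seen. What is missing is an automatic flag, since the 80% limit passes it, and last-dose time is not listed among the visit procedures.

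None of this removes the mismatch of 20 days against 17 plates.

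**Conclusion.** The inconsistency at Interview 3 is real. Supply and recovery rules as written cannot deliver daily dosing over every interval the windows allow. The shortfall is at most three doses, under windows anchored to study weeks (as stated for these visits), the visit-day dose taken from the new pack, and no carry-over. The share affected is about 6% to 12% depending on the assumed spread of visits. The effect is a small bias towards no difference in secondary week-4 endpoints.

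The safety-period shortfall (up to 3 days from Interview 5 to 6, up to 7 days between later visits) is conditional on study-week anchoring and on nine weeks meaning 63 daily doses. Minor severity.

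**What to change.** - Reconcile the visit-window, dispensing and drug-recovery text (Protocol summary, flow chart, sections 5.3.3 to 5.3.7, 6.4.2 and 6.5) so that the drug available covers every interval the windows allow. Which of these to change is for the sponsor and investigators to decide.
- State whether safety-period windows run from the study week or from the previous visit, and make that agree with the week-64 window.
- Record the time of the last dose with each blood pressure reading, so that non-trough readings can be identified.

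The cost is a wording change in these sections and one data field. It needs no extra visit or patient. Whether packing or dispensing changes depends on how the passages are reconciled.
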